**Methods:**

Health care units involved in the study are from primary care in Lohja, Southern Finland: home care (191 consented clients), the public healthcare center, and a private community pharmacy. System based risk management theory and action research method was applied to construct the collaborative procedure utilizing each profession’s existing resources in medication risk management of older home care clients. An inventory of clinical measures in usual clinical practice and systematic review of rigorous study designs was utilized in effectiveness study design.

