#### Randomization

Participants were randomized to an intervention group (IG) and a control group (CG) receiving standard home care. To prevent contamination between IG and CG and subsequent dilution of the intervention, participants were randomized by home care areas (2 areas to the IG, 3 areas to the CG) since each home care area has its own nursing staff. The randomization was performed by sealed envelopes. The study is considered as open-label. The IG (*n* = 104) received the intervention (CoMM) during the first year, while the CG (*n* = 87) received standard care and received the same intervention after the first year (delayed intervention as control).

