#### Participant timeline

Selected study period was 2 years with measurements at baseline (in 2015), and at 12 (in 2016) and 24 months (in the end of year 2017).

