#### Statistical methods

Data will be analyzed on an intention to treat principle, including all randomized participants in the group to which they were randomly assigned. Also per protocol analysis to compare participants from intervention group with clinically significant medication changes conducted due to CMR, MR or PR, with control group will be performed.

The effectiveness of intervention compared to controls receiving standard home care will be first analyzed with unadjusted analysis. If there exists any group differences in participant characteristics or clinical outcomes at baseline, these variables will be included in adjusted analysis.

Descriptive statistics (mean, median or percentages as appropriate) will be used to summarize the participant characteristics and clinical outcomes. The comparison in the participant characteristics and clinical outcomes at baseline between groups will be done by two-sample t-test for normally distributed variables and by Mann-Whitney U-test for non-normally distributed variables. Chi-square test will be used for categorical variables.

Continuous outcomes will be analyzed with analysis of variance or covariance and repeated measures analysis of variance or covariance. Dichotomous outcomes will be analyzed by binary logistic regression and ordinal outcomes by cumulative logistic regression using generalized estimating equations to account for the correlation between the repeated measurements. Participants with baseline measurement and at least one follow-up measurement will be included in longitudinal analysis. Two-sided statistical tests with a 5% level of significance will be used.

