The strength in using an action research method [21] in model development lies in its ability to consider practical challenges and produce solutions, considering existing resources. The method contributed to the step by step construction of the CoMM model and description of the responsibilities of each professional involved in the model, which is missing in many other studies [27]. Transferring the model to other home care localities is possible, but will require long term effort from a qualified coordinator, committed personnel and managers to reach the mature stage of the collaboration that is necessary for sustainable changes in working patterns.

This study produced a RCT with a combination of outcome measures to assess general health status and functional ability of the older adults, but also targeted to symptoms suggestive of adverse effects of medications. DRP-RAT is used as an outcome measure to evaluate potential decreases in clinically significant DRPs. Medication lists are used to investigate changes in the quality of medications (e.g., use of PIMs). According to previous evidence, a selected study period of 2 years should be long enough to demonstrate potential changes in study participants’ health outcomes, use of health services and sustainability of changes made in their medications.

The developed CoMM procedure is feasible for screening and reviewing medications of a high number of older home care clients to identify clients with severe DRPs and provide interventions to solve them utilizing existing primary care resources. The coordinating pharmacist was needed to facilitate the construction of new processes and introduce new tools and approaches in medication management of the older home care clients.

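### Controls receive CoMM after month 12, but the analysis against standard care is not limited to the 12-month follow-up

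*Protocol article*

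**What the plan says.** All references are to the protocol article.

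- **Randomization.** The intervention group "received the intervention (CoMM) during the first year". The control group "received standard care and received the same intervention after the first year (delayed intervention as control"). The section does not say what the intervention group receives in year 2. Allocation was by area: "participants were randomized by home care areas (2 areas to the IG, 3 areas to the CG"), giving 104 and 87 clients.
- **Participant timeline.** There are "measurements at baseline (in 2015), and at 12 (in 2016) and 24 months (in the end of year 2017"), so there are two post-baseline visits, one on each side of the controls' switch.
- **Statistical methods.** "The effectiveness of intervention compared to controls receiving standard home care will be first analyzed with unadjusted analysis". Continuous outcomes go to ANOVA or ANCOVA and their repeated-measures versions. Dichotomous and ordinal outcomes go to logistic models with GEE. The principle is intention to treat, and one follow-up value in addition to baseline is enough to enter the longitudinal analysis. No time point is named for the effectiveness contrast, and the switch is not mentioned.
- **Discussion.** It says that "a selected study period of 2 years should be long enough to demonstrate potential changes in study" participants' health outcomes and use of services, and also to show whether medication changes last.

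**The concern.** The stated comparator is absent at one of the two follow-ups. Up to month 12 the groups differ as CoMM versus standard care. At month 24 both have had CoMM, the controls more recently. Under intention to treat the treated controls still count as controls, so a model run over both visits, with no contrast named, can combine two different questions in one group effect. A client with only a 24-month value has no follow-up observation from the period when standard care existed, yet qualifies for the analysis.

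The trial's main conclusion is at stake. If CoMM works, a pooled estimate would understate it. A small 24-month difference could be reported as an effect that faded, when it may only show that controls had caught up.

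**Working it through.** **Figures in the plan.** The article states that no sample size calculation was made and gives no effect size or power, so there is no figure to reproduce. The group sizes agree with the abstract: 104 + 87 = 191, matching "home care (191 consented clients").

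**Inputs from the article.** n = 104 and 87; two-sided 5% level; visits at baseline, 12 and 24 months.

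**Assumptions (not in the article).** The 12-month effect is d = 0.4 SD (range 0.3 to 0.5). The correlation between the 12- and 24-month values is rho = 0.5 (range 0.3 to 0.7). A share f of the 12-month difference remains at 24 months: f = 1 is no catch-up, 0.5 half catch-up, 0 full catch-up. Clustering by area and dropout are ignored, so absolute powers are optimistic. The comparison between rows is what matters.

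**12-month contrast.** SE = sqrt(1/104 + 1/87) = 0.1453. z = 0.4/0.1453 = 2.753. Power = Phi(2.753 - 1.960) = Phi(0.793) = 79%.

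**Group effect pooled over both visits.** The effect is d(1 + f)/2 and the SE is 0.1453 x sqrt((1 + rho)/2). At rho = 0.5, SE = 0.1453 x 0.866 = 0.1258.

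- Full catch-up: effect 0.20, z = 1.590, power = Phi(-0.370) = 36%.
- Half catch-up: effect 0.30, z = 2.384, power = Phi(0.424) = 66%.
- No catch-up: effect 0.40, z = 3.179, power = Phi(1.219) = 89%.

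| d = 0.4 | Share of 12-month effect | Power, rho = 0.3 / 0.5 / 0.7 |
|---|---|---|
| 12 months only | 100% | 79% |
| Pooled, no catch-up | 100% | 93% / 89% / 85% |
| Pooled, half catch-up | 75% | 73% / 66% / 61% |
| Pooled, full catch-up | 50% | 40% / 36% / 32% |

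For d = 0.3 / 0.4 / 0.5 at rho = 0.5, power is 54% / 79% / 93% at 12 months. Pooled with full catch-up it is 22% / 36% / 51%.

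**24-month contrast alone.** It estimates f x d, which is zero under full catch-up.

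**Group-by-time test.** Take changes from baseline with equal correlation 0.5 among all three visits, d = 0.4 and f = 0. The noncentrality of the 2-df test is 0.4^2 / (0.75 x 0.1453^2) = 10.1, giving power 82%, against 79% for the 12-month change contrast. This test keeps its power because it responds to a difference that appears at month 12 and disappears by month 24. For the same reason, a significant overall result does not say that CoMM beat standard care at month 12.

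**The case against.** The strongest reply is that the diluting contrast is not written into the plan. Statistical methods names families of models. It does not say that visits are pooled or that a group main effect is the test. The simple ANOVA or ANCOVA could be run at 12 months alone, and only 12 months fits a comparator on standard care. A repeated-measures analysis with baseline is often read through its group-by-time term, which loses no power here. Visit-specific contrasts are also commonly settled in an SAP, which is not at hand.

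Most of this stands, and it limits the point. A reader might infer that the planned analysis is biased toward no effect as it is. The article does not support that, because the bias depends on a choice it leaves open. Nor does the text establish a fall to about a third of full power, which needs both pooling and full catch-up, or a reversed 24-month difference, which is possible but not shown. In a model with group-by-time terms read at month 12, a client with only a 24-month value does not corrupt the contrast.

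A reader might also take the Discussion as claiming two years of controlled evidence. It does not: the same sentence names sustainability of medication changes, a proper use of the 24-month data, and Randomization openly describes the delayed intervention.

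The reply does not remove the mismatch. The article defines the comparison by a comparator that its own design withdraws before the second follow-up, and its inclusion rule lets that follow-up stand alone. That is an inconsistency in what is stated, beyond detail left for later.

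**Conclusion.** The point holds in conditional form. The comparison with standard care exists only at month 12, and the article does not confine its effectiveness analysis to that visit. An analyst following the text could pool or report a 24-month contrast that has no standard-care arm.

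If visits are pooled, the estimate is (1 + f)/2 of the 12-month effect: 75% under half catch-up and 50% under full catch-up. With d = 0.4 and rho = 0.5, power is about 66% and 36% respectively, against 79% at 12 months. Effect size, correlation and degree of catch-up are assumptions, and clustering and dropout are ignored. The direction is firmer than the size: any catch-up shrinks a pooled or 24-month estimate. An analysis read at month 12 is not affected.

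**What to change.** **Statistical methods.** State that effectiveness versus standard care is the between-group contrast at 12 months, estimated from the longitudinal model with group, time, group x time and baseline. Label any 24-month between-group result as early versus delayed CoMM. Report two further analyses separately and mark them as non-randomised: durability from 12 to 24 months within the intervention group, and change within the control group after delayed CoMM.

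**Discussion.** Say that only the first 12 months are controlled against standard care, and that the second year addresses sustainability.

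A single model with time-varying CoMM exposure is not a ready substitute, because the article does not state the intervention group's exposure in year 2.

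**Cost.** Wording only. The trial gives up a controlled 24-month claim, which the design does not support.

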#### Participant timeline

Selected study period was 2 years with measurements at baseline (in 2015), and at 12 (in 2016) and 24 months (in the end of year 2017).

#### Sample size

The study sample was all home care clients, meeting inclusion criteria and giving voluntary informed consent, in the Lohja Home Care Unit due to the practical, administrative and financial issues. Sample size calculations were not performed.

#### Outcome measures

Selected primary outcome measures assess appropriateness of the medications used, general health status and functional ability of the older adults, but also target to specific symptoms that can be potentially caused as adverse effects of medications (Table 1). Majority of selected clinical measures were used in usual clinical practice in Lohja Home Care. Medication-specific measures include assessment of clinically significant DRPs by using DRP-RAT [31] and electronic screening tools (SFINX, Salko) for identifying PIMs for the older adults, anticholinergic and serotonergic load and clinically significant drug-drug interactions (DDIs) [32, 33]. Medicines will be classified according to the anatomical therapeutic chemical (ATC) classification system [34]. Use of health services will be measured as visits to physicians, frequency of visits of home care personnel and frequency of hospital days and will be used as a secondary outcome.

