**Fig. 3 Fig3:**
[figure not shown]
Developed coordinated medication management model (CoMM) for older home care clients

**Table 1 Tab1:** Agreed tasks of each healthcare professional and tools used in the coordinated medication management model (CoMM)

Healthcare professionals	Tasks in the coordinated medication management model	Tools used
Home care nurses (practical nurses, nurses)	Medication reconciliation Medication risk assessments Clinical tests to assess clients’ functioning and disability (at baseline, 12 and 24 month follow-up)	Medication lists, usual home visits Clinical interviews with the DRP-RAT a) Measures used in usual clinical practice: functional ability (RAVA) [37], physical performance (The five-times-sit-to-stand test) [38, 39], cognitive functioning (MMSE) [40], depression (GDS-15) [41] and malnutrition (MNA) [42]. b) Added measures: difficulties related to urination (UDI-6) [43], orthostatic hypotension (3 min test) [44] and alcohol use (AUDIT-C) [45].
	Implementing medication changes and monitoring their outcomes	Regular home visits as usual Informing physicians when needed
Community pharmacists	Prescription review (PR)	Clinically significant drug-drug interactions (DDIs) (SFINX) [32] Potentially inappropriate medicines (PIMs) according to Beers 2015 criteria [46], anticholinergic and serotonergic loads of medicines (Salko) [33].
	Medication review (MR)	Patient information: medication list, DRP-RAT and glomerulus filtration rate (GFR) results Other tools used: SFINX (DDIs), Pharao (Cumulative scoring of the anticholinergicity, bleeding risk, constipation, orthostatic hypotension, prolongation of QT interval, nephrotoxicity, sedation, convulsion risk and serotonergicity of the patient’s medication) [47], Salko (PIMs) [33], Renbase (Renal function and appropriateness of doses/medicines used) [9].
	Comprehensive medication review (CMR) conducted by a qualified pharmacist (TT, SL)	Patient information: medication list, DRP-RAT and GFR results, diagnosis, laboratory test results. Tools used: As in MR, complemented by client’s clinical interview [20, 48]
Coordinating pharmacist	Trainings of the PNs for the recruitment process, CoMM and use of DRP-RAT (MD)	Meetings, discussions, personal guidance, DRP-RAT training [29]

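### A multi-domain set of about 13 measures is designated primary, tests are at two-sided 5%, and no hierarchy or success rule controls the error rate of the superiority claim

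*Protocol article*

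**What the plan says.** The Trial design section describes a superiority trial with two parallel groups. Outcome measures defines the primary outcomes in the plural and by domain: "Selected primary outcome measures assess appropriateness of the medications used, general health status and functional ability of the older adults", continuing "but also target to specific symptoms that can be potentially caused as adverse effects of medications (Table 1").

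Table 1 lists the clinical tests. Five are already in routine use: "functional ability (RAVA) [37], physical performance (The five-times-sit-to-stand test) [38, 39], cognitive functioning (MMSE) [40], depression (GDS-15) [41] and malnutrition (MNA) [42"]. Three are added: "difficulties related to urination (UDI-6) [43], orthostatic hypotension (3 min test) [44] and alcohol use (AUDIT-C) [45"].

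Outcome measures then describes the medication side: "Medication-specific measures include assessment of clinically significant DRPs by using DRP-RAT [31] and electronic screening tools (SFINX, Salko"), the latter "for identifying PIMs for the older adults, anticholinergic and serotonergic load and clinically significant drug-drug interactions (DDIs) [32, 33"].

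The only outcome called secondary is use of health services, counted as physician visits, "frequency of visits of home care personnel and frequency of hospital days and will be used as a secondary outcome".

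Statistical methods gives one significance rule: "Two-sided statistical tests with a 5% level of significance will be used". It states no order of testing, no adjustment for several primaries and no definition of a positive trial. The Sample size section says that no calculation was done, so no power statement points to a lead outcome either.

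**The concern.** A superiority trial needs a stated result that decides the question. Here several outcomes from different domains share the primary label, and the stated level applies to each test, not to the set. If CoMM has no effect, the chance that some primary outcome reaches significance is well above 5%. Any favourable measure could then be reported as the trial's primary finding. The Dissemination policy allows separate papers on primary and secondary outcomes, which makes selective emphasis easier.

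The set also mixes measures close to the model's purpose, such as drug-related problems and inappropriate prescribing, with measures much further from it, such as nutrition or cognition. A reader of the results would have no advance basis for weighing one against another.

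**Working it through.** **Plan's own figure.** None. The article gives no family-wise error rate, power or sample size to reproduce.

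**Step 1: count the primaries.**
- Table 1, routine measures: RAVA, five-times-sit-to-stand, MMSE, GDS-15, MNA = 5.
- Table 1, added measures: UDI-6, orthostatic test, AUDIT-C = 3.
- Outcome measures section: DRP-RAT, PIMs, anticholinergic load, serotonergic load, DDIs = 5.
- Total 5 + 3 + 5 = 13. This count is read from the text; the article has no numbered endpoint list.

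**Step 2: assumptions.** One test per outcome, each with a true two-sided size of 5%, and no effect of CoMM on any outcome. The article gives no correlations between outcomes, so a common pairwise correlation r is assumed and varied.

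**Step 3: independent outcomes.**
- At least one significant result in either direction: 1 − 0.95^13 = 1 − 0.513 = 0.487.
- At least one result falsely favouring CoMM (0.025 in that tail): 1 − 0.975^13 = 1 − 0.720 = 0.280.

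**Step 4: correlated outcomes.** Write each test statistic as √r·U + √(1−r)·e, with U shared and all terms standard normal. Average over U the probability that all 13 statistics stay inside the critical limit 1.96, and subtract the average from 1. For the favourable direction only the one limit applies.

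| r | Either direction | Falsely favourable |
|---|---|---|
| 0 | 48.7% | 28.0% |
| 0.3 | 41.8% | 21.4% |
| 0.5 | 33.4% | 16.7% |
| 0.7 | 24.1% | 12.0% |
| 0.9 | 13.8% | 6.9% |
| Nominal, one test | 5% | 2.5% |

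**Step 5: sensitivity to the count.** Either direction, independent outcomes:
- 12 measures (for example, without AUDIT-C): 1 − 0.95^12 = 46.0%.
- The 8 clinical measures only: 1 − 0.95^8 = 33.7%.

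**Step 6: after a fix.** One named primary gives 5%. With Holm over 13, the first step is 0.05/13 = 0.0038, and the family-wise rate is at most 5% under any correlation.

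**The case against.** **The count is inferred.** Table 1 sets out professional tasks and tools; it is not an endpoint list. AUDIT-C fits the stated domains least clearly, so a reader might infer that alcohol use has been formally ranked beside inappropriate prescribing. The text does not settle that. This stands, and it is why the count is given as about 13. It does not rescue the plan, because the eight clinical measures alone give 34% if independent.

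**The either-direction figure overstates the harm.** Selective reporting of benefit concerns only results that favour CoMM, and the range 33% to 49% further assumes correlations of 0.5 or less. Both points stand. The favourable-direction figures are roughly half as large, and they are still well above 2.5%.

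**Further analyses.** A reader might multiply the tests again by two follow-up times, adjusted and unadjusted models, and two analysis sets. The document does not support that count. Adjustment is conditional on baseline differences, and the per protocol comparison reads as supplementary to intention to treat. The repeated-measures and GEE models may combine the time points. By 24 months the controls have also been offered CoMM, so that time point is not a plain comparison with standard care. None of this enters the figures above.

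**Left to the analysis plan.** An adjustment method may sit in a plan that is not shown, and the 5% sentence can be read as a generic nominal level. So it cannot be said that no adjustment will ever be made. But which outcomes are primary is a protocol decision. This article makes it, as a set with no deciding member.

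**Conclusion.** The point holds. As written, the primary claim has no controlled error rate, because several domains are primary together, the tests are at two-sided 5% and no rule says when CoMM counts as effective.

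For 13 measures the chance of at least one false primary result is 49%, 33% and 24% in either direction at correlations of 0, 0.5 and 0.7. For results falsely favouring CoMM it is 28%, 17% and 12%. These sizes rest on the inferred count, on assumed equal correlations, and on one correctly sized test per outcome. The conclusion does not depend on the exact values: with 13 measures, even a correlation of 0.9 leaves both rates at nearly three times nominal.

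The document does not show that every primary will in the end be judged alone without adjustment. It shows that nothing stated prevents this.

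**What to change.** **Preferred.** In Outcome measures, name exactly one primary outcome at 12 months, before controls receive CoMM, that matches the aim of reducing clinically significant drug-related problems. One example is clinically significant DDIs per client; another is PIMs per client. Only one of them should be chosen, because together they are two outcomes. SFINX and Salko are also tools of the intervention, so such a measure sits close to what CoMM acts on directly, and the article should say so. All other measures become secondary.

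**Alternative.** Keep several primaries, list them by name, apply Holm across the listed number (first step 0.05/13 = 0.0038 if there are 13), and report all of them together.

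**Timing.** The study is open-label, with 12-month measurement in 2016 and the last at the end of 2017, and Table 1's notes already mention March 2017. The choice should therefore be recorded with a date before any between-group analysis. If that is no longer possible, it should be declared post hoc.

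**Cost.** No new data are needed. Fewer claims can be made at nominal 5%. Holm lowers power for each outcome, which matters with 191 participants and no sample size calculation. The change may also count as an important amendment, which under Protocol amendments requires new ethical approval.
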